### Effectiveness outcomes and study measures

2.5

Participants will complete enrollment and baseline data collection before being randomly allocated the assignment to one of the two study arms. Participants will receive a random assignment through the prepared envelopes to Treat4All or UC at a ratio of 1:1. Masking of participants and intervention counselors to study arm assignment in the field is not feasible because of the nature of the interventions; data collection staff, analysts, and investigators will be masked to the study assignment until analyses are complete. Participants will be followed up for 6 months (Table 1).

**Table 1 tab1:** Schedule of enrollment, interventions, and assessments.

Timepoint	Enrollment	Baseline	Allocation	Post-allocation		
	*t_0_*	*t_0_*	*t_0_*	*t_0_*	Month 3	Month 6
Enrollment						
Eligibility screen	X					
Informed consent	X					
Random group allocation			X			
Intervention						
Treat4ALL						
Usual care						
Assessments						
Quantitative survey						
Sociodemographics and alcohol coping skills		X				
Readiness to change alcohol use Social desirability, sexual risk, HIV testing history, PrEP use history, PrEP knowledge and willingness, and ART initiation		X			X	X
HIV-related stigma, depression, health status, quality of life					X	X
Qualitative interviews (Treat4All arm only)						X
Primary outcomes						
Heavy drinking days (TLFB)		X			X	X
Engagement in HIV prevention (PrEP use) or treatment (viral suppression)		X				X
Secondary outcomes						
All participants						
PEth level^*^		X				X
STI prevalence		X				X
People with HIV only						
Viral suppression		X				X
ART adherence		X			X	X
People at risk for HIV only						
PrEP use		X				X
HIV incidence						X

^*^Dried blood spots will be collected from all participants.

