Following our theoretical premise that TrEAT will impact HIV prevention and treatment behaviors, we define our co-primary outcome of successful engagement in HIV prevention or treatment with parallel behaviors across HIV status: PrEP use for people at risk of HIV and viral suppression for PWH at 6 months. *PrEP use will be defined as a self-report of >1 pill in the past seven days a month 6. Viral suppression will be defined as an undetectable viral load (<40 copies/mL) at month 6*. Our primary outcome will not be stratified by HIV status. However, we will also assess viral suppression and PrEP use separately among PWH and those at risk for HIV, respectively, as secondary outcomes. In this way, we will assess the short-term efficacy of Treat4All among all participants (inclusive of HIV status) and separately among PWH and those at risk for HIV.

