### Data analysis

3.1

We will first explore the distribution of continuous and categorical baseline variables using descriptive statistics and graphical representations, as appropriate (60). We will then conduct intent-to-treat comparisons between arms, using a log link and binomial error distribution to compare the proportion of heavy drinking days and engagement in HIV prevention or treatment (co-primary outcomes). For the proportion of heavy drinking days, we will estimate the self-reported percentage of heavy drinking days measured by the TLFB at 6 months. We will evaluate the extent to which mean values differ across groups using the deviance χ^2^ (61). As the effect of the intervention may differ by age and sex, effect modification by these factors will be examined. For successful engagement in HIV prevention or treatment, the design effect introduced by participant randomization will be addressed using a robust variance estimate. Probability ratios (PR), analogous to prevalence ratios at a specific time point, with 95% confidence intervals, will be used to estimate and compare the proportion of participants in each arm who achieved the outcome (successful engagement in HIV prevention or treatment) at 6 months. All analyses will also be sex-stratified to explore differences by sex to inform power calculations for a future implementation effectiveness trial. A significance level of 0.05 and two-sided 95% CIs will be used with no adjustment for multiple testing (62).

Additional analyses will assess self-reported ART adherence (among PWH), biologically confirmed HIV incidence (among HIV-negative participants), PrEP use (among HIV-negative participants), viral suppression (among PWH), and biologically confirmed STIs (among all participants). We will also assess the possibility of selective differential attrition across the arms at each post-baseline visit. We will estimate and compare an *a priori* set of baseline demographics by the study arm. If an imbalance is found, we will produce post-baseline regression-adjusted outcome estimates by recalibrating the baseline distribution of that group to the baseline distribution across all groups combined (63).

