### Power considerations and sample size calculations

3.2

Our study will provide short-term efficacy data to inform a future, large-scale RCT. All tests will be based on a nominal 5% two-sided type I error, and confidence intervals will have a nominal 95% coverage. The main analysis on which our sample size calculation for the quantitative analysis was based is the short-term efficacy of the experimental intervention, Treat4All, vs. UC. Using two-tailed tests and *α* = 0.05, we will have >80% power to detect a difference as small as 16% points (e.g., 80% vs. 96%) with a sample of 144. To account for possible loss-to-follow-up/dropout of 10% based on our previous studies among patients receiving STI care in Malawi, we will inflate the sample size to 160 (*n* = 80 per arm [stratified 1:1 by HIV status]). While a sample size of 160 may limit generalizability, it is appropriate for this pilot study, which aims to assess feasibility and estimate effect sizes to inform a future, fully powered trial, in line with established guidance for early-phase research and prior pilot studies in similar contexts (64, 65). Sample size calculations were conducted using SAS 9.4, which will also be used for all statistical analyses.

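### Allocation is stated to be stratified by HIV status, but the HIV-engagement co-primary comparison leaves HIV status out, so its standard error is too large if success rates differ between the strata

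*Protocol article*

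**What the plan says.** - **Allocation.** Power considerations and sample size calculations gives "80 per arm [stratified 1:1 by HIV status" (closing bracket omitted). Effectiveness outcomes and study measures describes the procedure without naming strata: "Participants will receive a random assignment through the prepared envelopes to Treat4All or UC at a ratio of 1:1".
- **Outcome.** The second co-primary is a success/failure endpoint at 6 months. Its content depends on HIV status: a laboratory result (undetectable viral load) for people with HIV, and self-reported PrEP use for those at risk. The section then states "Our primary outcome will not be stratified by HIV status", and adds that each component will also be assessed in its own group as a secondary outcome.
- **Analysis.** Data analysis specifies a log link with binomial error and a robust variance. Probability ratios with 95% confidence intervals "will be used to estimate and compare the proportion of participants in each arm who achieved the outcome". No HIV-status term is named. Regression adjustment is foreseen only if baseline demographics turn out imbalanced. Effect modification is planned for age and sex.
- **Planning figure.** The article claims more than 80% "power to detect a difference as small as 16% points (e.g., 80% vs. 96%) with a sample of 144", inflated to 160 for 10% dropout. It gives no success rate by HIV status.

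**The concern.** Stratified allocation removes the between-stratum part of the variation from the comparison of arms. An analysis that ignores the strata still charges that variation to the standard error. Here the omitted factor also decides which outcome a participant is measured on, so different success rates in the two halves are plausible. The eligibility criteria point the same way. At-risk participants must be essentially off PrEP at entry, whereas people with HIV may qualify on a history of unsuppressed viral load within two years, so some may already be suppressed.

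The two safeguards in the article do not reach the problem. The robust variance is offered against a design effect attributed to participant randomisation, but it does not recover precision gained by stratifying. The imbalance-triggered adjustment concerns demographics, and HIV status would be balanced by design.

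At stake are intervals wider than the design warrants and lost power, in a pilot meant to supply effect estimates for a larger trial.

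**Working it through.** **Inputs from the article.** Two-sided 5% level; 80% vs 96%; 144 evaluable, so 72 per arm; 160 randomised, so 40 per arm per HIV stratum, and 40 × 0.9 = 36 evaluable. **Assumed:** all rates by stratum.

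**The article's own figure.** Power for 80% vs 96% at 72 per arm is 84.8% by normal approximation and 82.0% by Fisher's exact test. 144 / 0.9 = 160. The stated power and sample size reproduce.

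**Formulas.** Let p be an arm's overall rate and p_s its rate in stratum s (two equal strata of 36).

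- Crude variance of the log probability ratio: sum over arms of (1 − p) / (72p).
- Stratified variance: sum over arms of [Σ p_s(1 − p_s) / 36] / 4 / p², that is, Σ p_s(1 − p_s) / (144p²).

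**At 80% vs 96% overall.**

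- Crude: 0.20/57.6 + 0.04/69.12 = 0.00347 + 0.00058 = 0.00405; SE 0.0636.
- Equal rates in the strata: the stratified SE is the same; ratio 1.00.
- Control 70/90, treated 92/100: 0.30/(144 × 0.64) + 0.0736/(144 × 0.9216) = 0.00326 + 0.00055 = 0.00381; SE 0.0617; ratio 1.03.
- Widest possible split, control 60/100, treated 92/100: 0.24/(144 × 0.64) + 0.00055 = 0.00260 + 0.00055 = 0.00316; SE 0.0562; ratio 1.13.

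**At lower assumed usual-care rates, with +16 points in each stratum.** SEs are from the formulas. Power is from 200,000 simulated trials per setting, where that was run.

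| Control rates (suppression/PrEP) | Crude SE | Stratified SE | Ratio | Power, crude to stratified |
|---|---|---|---|---|
| 50/20 | 0.1978 | 0.1881 | 1.05 | 50% to 52% |
| 60/20 | 0.1782 | 0.1628 | 1.09 | 50% to 56% |
| 60/10 | 0.1978 | 0.1695 | 1.17 | not simulated |
| 70/10 | 0.1782 | 0.1412 | 1.26 | 50% to 69% |

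**Type I error of the crude test (no effect in either stratum).** At 70/10 the crude variance is 2 × 0.60/(72 × 0.40) = 0.0417, SE 0.204. The stratified variance is 2 × 0.30/(144 × 0.16) = 0.0260, SE 0.161. The ratio is 1.265, so the effective critical value is 1.96 × 1.265 = 2.48 and the size about 1.3%. Simulation gives 1.3% crude and 4.8% stratified at 70/10, and 3.2% crude and 4.9% stratified at 60/20. At 50/50 the two tests coincide (5.5% each).

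**Does the robust variance help?** For a data table with control 60/20 and treated 76/36, the robust SE from a modified Poisson model is 0.178 without HIV status and 0.163 with it. The probability ratio is 1.38 in both. So the robust variance alone leaves the excess in place.

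**The case against.** **HIV status may yet be in the model.** The sentence on not stratifying can be read as saying only that the outcome is pooled, in contrast to the separate secondary outcomes, and a statistical analysis plan that is not shown could add the covariate. This is fair, and it limits the point to the article as written. But the article does specify link, error distribution, variance, effect measure and the trigger for adjustment, and a reader following it would leave HIV status out.

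**Stratified allocation rests on one parenthesis.** The envelope description names no strata. If allocation is not in fact stratified, the crude test keeps roughly its nominal size and the type I error figures above do not apply. This stands as a condition on the finding.

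**The loss may be small.** At the article's own overall rates a 70/90 split costs only 3% in the standard error. This also stands. The larger figures need lower and more divergent rates than the planning example.

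**Two stronger readings are tempting but not supported.** A reader might infer that the pooled ratio is wrongly dominated by the stratum with the higher success rate. It does weight strata by control-arm rate: 70% to 77% together with 10% to 20% gives (77 + 20)/(70 + 10) = 1.21, against stratum ratios of 1.1 and 2.0. But that is a valid marginal ratio, and standardising over equal strata gives the same 1.21. At an overall 80% control rate, the widest split weights the strata only 0.375/0.625. A reader might also infer that a response confined to one half would be hidden. The article already plans separate results for each group, so both would be seen.

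**Conclusion.** As written, the article stratifies on HIV status and then leaves it out of the co-primary comparison. The consequence is conservative: some lost precision and power, with no bias and no excess of false positives. It rests on three conditions: allocation is stratified as the sample-size section says, no HIV-status term enters the model, and usual-care rates differ between the strata. The excess in the standard error is 0% to about 13% at 80% vs 96% overall, and about 5% to 26% for assumed control rates from 50/20 to 70/10. The rates by stratum are assumptions throughout, and equal rates mean no loss. It is worth correcting because the remedy uses information already collected.

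**What to change.** Keep the pooled co-primary and state that HIV status, as the stratification factor, enters its analysis. Report a standardised or Mantel-Haenszel probability ratio and a risk difference, each with a stratified variance. Simply adding HIV status to the log-binomial model is less suitable, because it changes the estimate (1.38 to 1.31 in the 60/20 table above), whereas the modified Poisson ratio stays at 1.38.

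State in the allocation paragraph whether the envelopes are prepared separately by HIV status, so that it agrees with the sample-size section. Present the planned stratum-specific results beside the pooled one, with an arm-by-HIV-status estimate labelled exploratory; with about 36 evaluable per arm per stratum it would have little power as a test. Adjustment for baseline suppression among people with HIV is optional.

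The cost is wording only: HIV status and baseline viral load are already recorded, and the sample size does not change.

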### Retention

2.6

Based on recent HPTN clinical trials at the UNC Project-Malawi, we anticipate a 90% retention rate among participants (59). To maximize retention, the Malawi research team will apply the following procedures: (a) computerized follow-up program to track scheduled and missed study visits; (b) updating baseline locator information at a 1-month locator check-in; (c) contacting participants by mobile phone within 24 h of missed visit; (d) attempting home visits if contact by mobile phone was not successful; and if the participant has changed address, the information will be solicited (while maintaining confidentiality) from locator contacts provided by the participant. A participant will be considered lost to follow-up if five phone contacts and home visits are unsuccessful.

## Assessment of the preliminary effectiveness of Treat4All

3

### Data analysis

3.1

We will first explore the distribution of continuous and categorical baseline variables using descriptive statistics and graphical representations, as appropriate (60). We will then conduct intent-to-treat comparisons between arms, using a log link and binomial error distribution to compare the proportion of heavy drinking days and engagement in HIV prevention or treatment (co-primary outcomes). For the proportion of heavy drinking days, we will estimate the self-reported percentage of heavy drinking days measured by the TLFB at 6 months. We will evaluate the extent to which mean values differ across groups using the deviance χ^2^ (61). As the effect of the intervention may differ by age and sex, effect modification by these factors will be examined. For successful engagement in HIV prevention or treatment, the design effect introduced by participant randomization will be addressed using a robust variance estimate. Probability ratios (PR), analogous to prevalence ratios at a specific time point, with 95% confidence intervals, will be used to estimate and compare the proportion of participants in each arm who achieved the outcome (successful engagement in HIV prevention or treatment) at 6 months. All analyses will also be sex-stratified to explore differences by sex to inform power calculations for a future implementation effectiveness trial. A significance level of 0.05 and two-sided 95% CIs will be used with no adjustment for multiple testing (62).

Additional analyses will assess self-reported ART adherence (among PWH), biologically confirmed HIV incidence (among HIV-negative participants), PrEP use (among HIV-negative participants), viral suppression (among PWH), and biologically confirmed STIs (among all participants). We will also assess the possibility of selective differential attrition across the arms at each post-baseline visit. We will estimate and compare an *a priori* set of baseline demographics by the study arm. If an imbalance is found, we will produce post-baseline regression-adjusted outcome estimates by recalibrating the baseline distribution of that group to the baseline distribution across all groups combined (63).

If >10% of observations are missing for a particular endpoint, we will quantify the sensitivity of our results to our assumption that all missing values have not achieved the outcome of interest (i.e., they did not decrease heavy drinking or did not achieve HIV outcome). We will assess predictors of loss to follow-up and apply inverse probability of observation weights (IPOW) to assume that data are missing at random (MAR). When disseminating the results, we will present weighted and unweighted results and a description of the accompanying assumptions.

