We will collect detailed information on alcohol use through the Alcohol Timeline Followback (TLFB) to obtain the number of heavy drinking days, percentage of days abstinent, drinks per drinking day, and measure changes in drinking over time (51). This interviewer-administered assessment reconstructs a daily behavioral calendar to prompt memory recall for alcohol consumption. TLFB has demonstrated good test–retest reliability, convergent validity, and agreement with collateral reports on daily drinking (52, 53). Specific quantities of alcohol consumed will be collected for each day for the 21 days (mirroring the consumption time frame detected by PEth) prior to the baseline, 3, and 6-month assessments. Daily alcohol consumption will be recorded as the number of standard drinks consumed. In general, and as we have previously used in Malawi, 341 mL of beer, 142 mL of wine, 34 mL of liquor/commercial spirit, a 50 mL sachet of local spirit distilled from grains, sweet potatoes, or sugar cane, a 330 mL can of fruit ale, or a 1,000 mL packet of chibuku will equal one standard drink (54–56). An alcohol biomarker will be randomly ascertained in 25% of the participants to validate self-reports at 6 months. The *proportion of heavy drinking days in month 6 will be defined as the proportion of days of heavy drinking (≥4 drinks per day for men and ≥3 drinks per day for women) in the past 21 days*. DBS samples will be collected from all participants. Based on budgetary constraints, a subsample (25%) will be randomly selected for alcohol biomarker testing, equally distributed from the Treat4All or usual care arms. This approach allows for objective measurement of alcohol use while balancing feasibility within a pilot trial context. PEth results >20 ng/mL will be defined as evidence of recent heavy drinking (50, 57, 58). Participants who self-report <50% for heavy drinking days but have PEth results >20 ng/mL will be assigned a proportion of 50% for heavy drinking days within the previous 21 days (50).

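### Heavy drinking days are tested with a binomial deviance chi-square that ignores clustering of days within persons, while the robust variance goes to the co-primary outcome that has no design effect

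*Protocol article*

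**What the plan says.** Section 3.1 (Data analysis) places both co-primary outcomes under one model family, "using a log link and binomial error distribution to compare the proportion of heavy drinking days and engagement in HIV prevention or treatment". It then treats them separately.

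- **Heavy drinking days.** The test is a deviance chi-square: "We will evaluate the extent to which mean values differ across groups using the deviance". No scale parameter, robust variance or random effect is named for this outcome.
- **Engagement.** "For successful engagement in HIV prevention or treatment, the design effect introduced by participant randomization will be addressed using a robust variance estimate".

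Section 2.5 defines the two outcomes. For alcohol, "Specific quantities of alcohol consumed will be collected for each day for the 21 days" before each assessment, and the outcome is each person's share of those days that were heavy. A participant in the biomarker subsample whose self-report is below 50% but whose PEth is above the cutoff "will be assigned a proportion of 50% for heavy drinking days within the previous 21 days". Engagement is one yes/no value per person at month 6. Randomisation is of individual participants, 1:1 (section 2.5), in a single clinic (section 2.1).

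Section 3.2 promises a nominal 5% two-sided type I error and nominal 95% coverage for all tests and intervals. Section 3.1 makes no adjustment for multiple testing.

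**The concern.** A binomial error distribution for a share of 21 days is right only if a person's days are independent and everyone in an arm has the same daily probability of heavy drinking. Drinking is habitual and people differ, so the person-level proportions will spread more widely than a binomial allows. A deviance test with no dispersion correction takes its variance from the binomial and cannot see that extra spread.

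The plan does include a variance correction, but assigns it to engagement. That outcome has one observation per randomised person, so there is nothing to cluster, and individual randomisation produces no design effect. The reason given for the correction is wrong, and the outcome that does have clustered observations gets none.

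At stake are the p-value and confidence interval of the first co-primary outcome. The trial's stated purpose includes estimating effect sizes for a fully powered successor, and its sex-stratified analyses are meant to feed that trial's power calculation, so a wrong standard error would be carried forward.

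**Working it through.** **1. The plan's own figure.** Section 3.2 claims more than 80% power for 80% versus 96% with 144 evaluable (72 per arm). With the pooled test:

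- SE under the null = √(2 × 0.88 × 0.12 / 72) = 0.0542
- SE under the alternative = √((0.80 × 0.20 + 0.96 × 0.04) / 72) = 0.0525
- Power = Φ((0.16 − 1.96 × 0.0542) / 0.0525) = 84.8% (Fisher's exact test: 82.0%)
- 144 / 0.9 = 160

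Both figures reproduce. The calculation uses one yes/no value per person, so it does not bear on the variance of a 21-day proportion.

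**2. Inputs.** From the document: 21 days per person, 72 evaluable per arm, two-sided 5%. Assumed, because the document gives none: ICC of heavy drinking between days of the same person, 0.05 to 0.5.

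**3. Coding A: 21 binomial trials per person.** The design effect is DEFF = 1 + (21 − 1) × ICC. The true SE is √DEFF times the model SE. Type I error = 2 × (1 − Φ(1.96 / √DEFF)). Example at ICC 0.2: DEFF = 5, √5 = 2.24, 1.96 / 2.24 = 0.877, type I error 38%.

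| ICC | DEFF | True SE / model SE | Type I error | Coverage of nominal 95% CI |
|---|---|---|---|---|
| 0 | 1 | 1.00 | 5% | 95% |
| 0.05 | 2 | 1.41 | 17% | 83% |
| 0.1 | 3 | 1.73 | 26% | 74% |
| 0.2 | 5 | 2.24 | 38% | 62% |
| 0.3 | 7 | 2.65 | 46% | 54% |
| 0.4 | 9 | 3.00 | 51% | 49% |
| 0.5 | 11 | 3.32 | 56% | 44% |

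Beta-binomial simulation (72 per arm, 21 days, 20,000 null trials per setting) agrees with the formula to about one percentage point. In the same kind of simulation, with mean proportions 0.2, 0.3 and 0.5, a person-level robust variance on the log ratio gave 4.6% to 5.4% at every ICC.

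**4. Coding B: one fractional value per person, weight 1.** The model variance is now that of a single yes/no trial. The true variance is DEFF / 21 of it, so type I error = 2 × (1 − Φ(1.96 / √(DEFF / 21))).

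- ICC 0.3: 7 / 21 = 0.333, type I error 0.07%
- ICC 0.4: 9 / 21 = 0.429, type I error 0.3%
- ICC 0.5: 11 / 21 = 0.524, type I error 0.7%

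Power for an illustrative 40% versus 25% (assumed, not in the document):

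- Model SE = √(2 × 0.325 × 0.675 / 72) = 0.0781, so a difference of 1.96 × 0.0781 = 0.153 is needed.
- True SE = √((0.24 + 0.1875) × DEFF / 21 / 72), which is 0.0376 at ICC 0.2 and 0.0504 at ICC 0.4.
- Power under coding B = Φ((0.15 − 0.153) / true SE), about 47–48%; simulation gives 48–49%.
- Power with the correct variance = Φ(0.15 / true SE − 1.96) = 98% at ICC 0.2 and 84% at ICC 0.4.

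Coding A is correct only at ICC 0 and coding B only at ICC 1.

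**5. Engagement.** With 58/72 versus 69/72, the model-based SE of the log ratio is √((14/72)/58 + (3/72)/69) = 0.0629. The robust SE is also 0.0629. The robust variance changes nothing there.

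**6. PEth rule.** 50% of 21 days is 10.5 days, which is not a possible binomial count. The rule moves the data further from the assumed distribution.

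**The case against.** The strongest reply is that the article does not say the dispersion is fixed at 1 or that 21 trials per person are entered. A scaled deviance test is still a binomial-family, deviance-based test and would be acceptable, and such detail is often left to an analysis plan. The reference to mean values could also point to one proportion per person, in which case an uncorrected test is conservative and the inflation figures do not apply. The ICC range and the 40% versus 25% example are assumptions, and the conservatism of coding B fades as the ICC rises: at ICC 0.8, DEFF is 17 and type I error is about 3%. The robust variance on engagement is harmless, and the point estimates do not depend on the variance.

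Much of this is true, but it does not remove the point. The text is not merely silent: it names a test for one outcome and expressly attaches the variance correction to the other, for a reason that does not hold. An analysis plan faithful to it would repeat the error. Nothing in the article indicates a scaled test. The coding decides the direction of the error, not whether there is one. That the trial is a pilot does not help, since its variance estimates are meant to inform the next trial.

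**Conclusion.** The point stands and should be corrected before analysis. As written, the test and interval for heavy drinking days do not deliver the nominal 5% error and 95% coverage promised in section 3.2. If day counts are modelled, type I error is about 17% at ICC 0.05 and 51% at ICC 0.4, and intervals are too narrow. If one fractional value with weight 1 is modelled, type I error is below 0.5% up to ICC 0.4, intervals are too wide, and roughly half the power is lost in the example used. These sizes rest on the assumed ICC range, on 72 evaluable per arm, and on no dispersion correction being applied, since none is stated. The fault is confined to heavy drinking days. For engagement only the stated rationale is wrong.

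**What to change.** In section 3.1, and in the analysis plan if one exists:

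- State that heavy drinking days at month 6 are analysed with one record per person, using a fractional log- or logit-link model with a robust (sandwich) variance, or a quasi-binomial or beta-binomial model. A beta-binomial likelihood needs whole counts, so the 10.5 days produced by the PEth rule fit more naturally with the fractional or quasi-binomial option.
- Replace the deviance chi-square with a robust Wald or score test of arm, or a scaled F test if the quasi-binomial model is chosen. Use the same variance for the effect-modification and sex-stratified analyses.
- Delete the statement that participant randomisation introduces a design effect. The robust variance may stay for engagement, where it does no harm.

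The cost is a few sentences and an option in the SAS call. No new data, visits or participants are needed, and the change can be made while analysts are still masked.
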